### Statistical analyses

Analysis will be both descriptive and comparative.

### Descriptive analysis

Differences in personal and disease characteristics will be compared between participants completing the study, those who fulfill the inclusion criteria but decline participation (primary drop-out), and those who participate in parts of the study but for various reasons end participation (secondary drop-out). We will investigate for specific characteristics that distinguish drop-out individuals from those who complete the study.

The included study population will be described and the intervention and control groups will be compared for eventual significant differences in personal and disease characteristics. 'Intention to treat' analysis will be used for comparing the efficacy of the two groups and longitudinal random effects regression models (panel analysis) will be applied.

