### Preparation day

The preparation day will take place seven days prior to the scheduled hospitalization. The overall purpose of the rehabilitation program will be explained and the individual areas for rehabilitation efforts will be defined in a collaboration between the patient and an appointed supervisor who serves as both the patient’s coach and as an 'orchestra conductor' for the rehabilitation team during the entire hospitalization. Prior to this preparation day, the patient will complete a FAMS form [16], a questionnaire on diet, smoking, alcohol and exercise, and indicate which of five focus areas is most important for him/her:

Energy level, including fatigue, scheduling, breaks and structure

Cognitive function, including memory, concentration and insight

Physical function, including walking, balance, endurance, strength and mobility

Psychological well-being, including strengthening coping mechanism, confidence, self-care, cognition and adjustment processes

Personal needs, including transferring, urination, toilet visits, bathing and medication.

The patient will also complete Form one in MYCaW [17,18]. The conversation follows clinical guidelines for target setting content and includes COPM [19-22] as identification and qualification of the decision basis for the objective. The conversation leads to identification of the primary goal within the five main areas (see above) and specific subsidiary goals and described cf. International Classification of Functioning, Disability and Health (ICF) classification of activity or participation level, supplemented by specific milestones [23].

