### Four-week hospitalization

A hospitalization period of 20 days is organized as four weeks of continuous hospitalization. A team of relevant professionals is composed based on the assessment of the patient's needs and may include neuropsychologist, clinical psychologist, occupational therapist, physiotherapist, nutritional therapist or dietitian, nurse, healthcare assistant, nursing assistant, social worker. The neurologist will carry out the primary standard neurological examination and serve as consultant for the patient and supervisor for the team. Symptomatic drug therapy is organized or administered after the usual guidelines and the neurologist’s judgment.

The patient’s supervisor is responsible for the content of the patient's program and should oversee that it contributes to the work of the team and patient, works towards the agreed objectives and milestones and that the necessary adjustments are made during hospitalization. The supervisor and the patient continuously evaluate the program, for example by weekly conversations, and at discharge. According to patients’ wish, relatives and other team members may participate in one or more of the conversations.

During the rehabilitation period process data are collected on selected specific rehabilitation interventions, their nature, number, duration and medication.

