### Data analysis

#### Sample size calculation

Determination of the required sample size is based on known data from the previous FAMS study [8,26]. The FAMS total score ranges from 0-170 and the average score at referral was 103 (SD 27). Assuming that a 5% score change indicates a clinically significant change, then the mean score should change to more than 108 i.e. that a clinically significant change requires a 5-point change.

To test a 5-point difference between two groups with 5% statistical significance (alpha) and 90% power (beta), the calculated required number of participants in each group is 613 people. With 80% power the required number of participants is reduced to 458.

If we want to test a 10-point difference, there needs to be 154 people (assuming 90% power) or 115 people (80% power).

The current study participants are expected to be a more homogeneous group than in the previous study, thus the variation in FAMS score is likely to be reduced. If the standard deviation is assumed to be 20 (instead of 27), then 252 patients will be needed in each group to identify a 5% difference with 80% power.

Taking into account correlation between repeated measurements for the same individual and assuming that the correlation between two subsequent measurements is 0.8, a 5-point difference could be identified with 160 participants (90% power) or 120 participants (80% power) in each group.

Based on these assessments a reasonable sample size is considered to be around 200 participants in each of the two groups. The Sclerosis Hospitals expects to admit 1,200 people with multiple sclerosis in the period March 2012 through June 2013. An unknown number will be either excluded from the study or will decline to participate in the study. If an insufficient number of patients has been recruited at the end of the planned inclusion period, a (short) extension of the inclusion period will be possible.

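### No allowance for supervisor clustering in the treated arm is made in the sample size or named in the model; if the six-month model has only a patient-level random effect and the intra-supervisor correlation is positive, its standard error is too small

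*Protocol article*

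**What the plan says.** All places are in the protocol article.

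- **Contrast.** *Comparative analysis* lists first the change from A1 to A5 in the intervention group against the change from B1 to B2 in the control group. *Data collection* describes B2 as the control measurement without intervention. *Methods and design* puts control admission at about eight months. So at six months only one arm has been treated.
- **Provider.** Under *Preparation day*, the areas for rehabilitation are set in "a collaboration between the patient and an appointed supervisor who serves as both" coach and leader of the team for the whole stay. Under *Four-week hospitalization*, the "supervisor is responsible for the content of the" programme and oversees its adjustment. The team is put together for each patient's needs.
- **Sample size.** The section uses an SD, a difference, alpha and power, and then one correlation, introduced by "Taking into account correlation between repeated measurements for the same individual" and set at 0.8. No correlation between patients appears.
- **Model.** *Descriptive analysis* says that "longitudinal random effects regression models (panel analysis) will be applied". It does not say at which level the random effects sit.

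**The concern.** When one person shapes the goals and content of treatment for several patients, those patients may share part of their outcome. Here that sharing can arise in one arm only, because controls have met no supervisor by B2. This is a partially nested design. A patient-level panel model deals with repeated measurements on a person but not with similarity between patients of the same supervisor.

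The contrast affected is the only randomised comparison of rehabilitation with no rehabilitation. At stake are the width of its confidence interval and, to a lesser degree, the powers given under *Sample size calculation*. A supervisor effect can be fitted only if the supervisor is recorded, and the process data listed under *Four-week hospitalization* do not mention that identifier.

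**Working it through.** **1. Reproduce the plan's figures.** For two means with two-sided alpha 0.05, 1:1 allocation and independent patients, n per group = 2·SD²·(1.96 + z_power)²/d², rounded up, where z_power is 1.2816 (90%) or 0.8416 (80%).

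- SD 27, d = 5: 612.8 and 457.7, so 613/458, as stated.
- SD 27, d = 10: 153.2 and 114.4, so 154/115, as stated.
- SD 20, d = 5, 80% power: 251.2, so 252. This matches "If the standard deviation is assumed to be 20 (instead of 27), then 252 patients will be needed in each group".
- Correlation 0.8: the article gives no formula. Baseline-adjusted analysis with two follow-ups multiplies the variance by f = (1 + 0.8)/2 − 0.8² = 0.26. With SD 27, n = 159.3 and 119.0, so 160/120, as stated.

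Every figure is reached with independent patients and no design effect.

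**2. Is sharing of supervisors plausible?** The article gives no number of supervisors. It expects 1,200 admissions from March 2012 through June 2013, which is 16 months or about 69.5 weeks. If all stays last four weeks and flow is steady, 1,200 × 4/69.5 ≈ 69 patients are in hospital at any time. With stable staff and trial patients spread evenly, one patient per supervisor at a time gives 200/69 ≈ 3 treated trial patients per supervisor. Three to four at a time gives about 9 to 12. Staff turnover would lower these numbers.

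**3. Effect on the contrast.** Let m be treated patients per supervisor and ρ the intra-supervisor correlation of the baseline-adjusted outcome. Both are assumptions. The treated arm's variance is multiplied by 1 + (m − 1)ρ and the control arm's by 1. At 1:1 the variance of the difference is multiplied by V = 1 + (m − 1)ρ/2, and true SE/naive SE = √V. If supervisor effects vary around a zero mean, the actual type I error of the naive test is 2·[1 − Φ(1.96/√V)].

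| m | ρ | V | √V | Type I error |
|---|---|---|---|---|
| 5 | 0.01 | 1.020 | 1.010 | 5.2% |
| 10 | 0.02 | 1.090 | 1.044 | 6.1% |
| 10 | 0.05 | 1.225 | 1.107 | 7.7% |
| 20 | 0.05 | 1.475 | 1.214 | 10.7% |
| any | 0 | 1 | 1 | 5.0% |

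A ratio of 1.214 means that the true SE is 21% above the naive one; equivalently, the naive SE is 1 − 1/1.214 = 18% below the true one.

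**4. Numbers and power on the plan's own basis** (SD 27, f = 0.26, so effective SD 27·√0.26 = 13.77).

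- Required n at m = 10, ρ = 0.05: 159.3 × 1.225 = 195.2 and 119.0 × 1.225 = 145.8, so 196/146 per group.
- Power at 200 per group, no clustering: SE = 13.77·√(2/200) = 1.377; Φ(5/1.377 − 1.96) = 95%.
- m = 10, ρ = 0.05: SE = 1.377 × 1.107 = 1.524; power 91%.
- m = 20, ρ = 0.05: SE = 1.377 × 1.214 = 1.672; power 85%.

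**5. Sensitivity.** The factor 0.26 needs two follow-ups, whereas the six-month contrast has one. With one follow-up, f = 1 − 0.8² = 0.36, and power at 200 per group is 87% without clustering and 80% at m = 10, ρ = 0.05. Most of the fall from 95% to 80% thus comes in about equal parts from the follow-up count and from clustering. The first is a separate matter.

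**The case against.** The strongest case against runs as follows.

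- **The model sentence contains no error.** It leaves the level of the random effects open, and an article may leave that to an analysis plan not shown here. This stands. A reader might infer from the words panel analysis that the model treats all patients as independent, but the text neither includes nor excludes a supervisor level.
- **The standard error is not shown to be too small.** That needs several patients per supervisor and a positive correlation, and the article gives neither. This stands; the size can only be a range, and it starts near nothing.
- **Teams.** A reader might extend the point to shared teams. Teams are composed for each patient, so they overlap and do not form nested clusters. The point rests on supervisors alone.
- **Type I error.** If rehabilitation affects nobody, there is no treatment effect to share and individual randomisation keeps the rate at 5%. Inflation needs supervisor effects that differ but average zero. This stands as a condition on the figures above.
- **Fixed supervisors.** The stated aim concerns the programme as these two hospitals provide it. If inference is limited to their existing staff, no inflation is due. That is a legitimate choice. But the *Discussion* wants the results to inform service development and health authorities, which looks beyond the supervisors who happened to be in post.
- **Timing.** Admission within two months and a four-week stay place A5 about three months or more after discharge, when a supervisor effect may have faded. That argues for the lower end of the range.
- **Power.** A reader might infer that the trial becomes underpowered. On the plan's own basis, about 200 per group keeps 85% power even at the top of the assumed range.

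What remains is that the sample size section sets out its correlation structure in detail and includes no provider component, in a design where only one arm has providers.

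**Conclusion.** The point holds in conditional form. It is confirmed that only the intervention arm has been treated at six months, that a supervisor steers each treated patient's programme, and that the stated sample sizes assume independent patients. Sharing of supervisors is a strong inference from the patient numbers, not a stated fact.

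If the six-month model has only a patient random effect and the intra-supervisor correlation is above zero, the true SE exceeds the naive SE by 1% to 21% over the assumed range, and by 4% to 11% at 10 patients per supervisor with correlation 0.02 to 0.05. The matter is mainly one of interval width. It is a worthwhile and inexpensive improvement to the plan, not a demonstrated error in it.

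**What to change.** 1. Record the supervisor's identifier for each admission.
2. In the six-month model, add a supervisor random effect that applies to intervention-arm follow-up observations only, with hospital as a fixed effect and a small-sample degrees-of-freedom correction, since the number of supervisors may be small.
3. Under *Sample size calculation*, say that the figures assume no supervisor clustering, and show them over a stated range of caseload and correlation (for example 160/120 becoming 196/146 at 10 per supervisor and 0.05).

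The cost is one variable, which the hospitals presumably hold already, and a few lines of text. The downside is a slightly wider confidence interval and a slightly less favourable stated power.

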### Comparative analysis

The following comparative analysis will be conducted:

Difference from Time A1 to Time A5 for intervention group compared with the difference from Time B1 to Time B2 for control group (i.e. difference in outcomes for rehabilitation vs. no rehabilitation at 6-month follow-up)

Difference between Time A1 and Time B1 (i.e. difference between intervention and control group at baseline)

Difference between Time A1 and Times A5 and A6 (i.e. baseline vs. 6- and 12-month follow-up for intervention group)

Difference between Time B3 and Time B6 for control group (i.e. admission vs. 12-month follow-up).

Difference between A2 and A3 for intervention group (pre- vs. post-hospital rehabilitation)

Difference between B3 and B4 for control group (pre- vs. post-hospital rehabilitation).

Difference between Time A1 and Time A4 for intervention group A (baseline vs. one month after hospital rehabilitation)

Difference between Time B3 and Time B5 for control group (pre- vs. one month after hospital rehabilitation)

Changes in Mastery (heiQ) over time: Times A1, A4, A5 and A6 for intervention group compared with Times B1, B2, B5 and B6 for control group

Subgroup analyses will be performed on the individual focus areas, based on data from participants who have completed the goal-related questionnaires.

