## Methods and design

The study is designed as a pragmatic clinical trial [9] of a complex intervention with personalized outcomes [10]. It attempts to maximize external validity by incorporating important features of the rehabilitation intervention in real-life settings and allowing individual participant-selected treatment goals and personalized outcomes.

The study design (Figure 1) is a two-hospital controlled trial of the rehabilitation intervention with randomization to either early admission (‘intervention group’; admission within two months after referral and clinical prescreening) or usual admission (‘control group’; admission approximately eight months after referral to the hospital and clinical prescreening). Any differences between these two groups on observed measures between baseline and six-month assessments will be considered as effects of the rehabilitation program. As the control-group patients are admitted to the hospitals after approximately eight months from referral and prescreening, they also contribute with data to the effect of personalized rehabilitation. To observe long-term effects, data collection will be repeated after twelve months.

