### Randomization

Randomization will be performed by staff at the admitting hospital using specialized computer software. To ensure balance between different patient groups, the randomization will be stratified according to gender, age (four groups), MS type (three groups), duration of diagnosis (five groups), EDSS score (three groups), and whether or not the patient is admitted to the hospital for the first time (two groups).

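### The six-month contrast is written as a difference in change with no stated adjustment for baseline or the randomisation factors, and the repeated-measures sample size does not fit a single follow-up

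*Protocol article*

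**What the plan says.** **Contrast.** The first item under Comparative analysis is "Difference from Time A1 to Time A5 for intervention group compared with the difference from Time B1 to Time B2 for control group". Methods and design gives it its causal reading: "Any differences between these two groups on observed measures between baseline and six-month assessments will be considered as effects of the rehabilitation program".

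**Model.** Descriptive analysis names intention to treat and random-effects regression for longitudinal data. It lists no covariates.

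**Baseline.** Comparative analysis lists the A1 against B1 difference as a comparison in its own right. Descriptive analysis adds that "the intervention and control groups will be compared for eventual significant differences in personal and disease characteristics".

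**Randomisation.** Under Randomization, "the randomization will be stratified according to gender, age (four groups), MS type (three groups"), followed by duration of diagnosis (five groups), EDSS (three) and first or repeat admission (two).

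**Sample size.** "The FAMS total score ranges from 0-170 and the average score at referral was 103 (SD 27"), and "a clinically significant change requires a 5-point change". Without repeated measurements the article gives 613 per group for 90% power and 458 for 80%. With a correlation of 0.8 between measurements it gives 160 and 120. It settles on around 200 per group.

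**The concern.** A difference in change subtracts the whole baseline value, although at a correlation below 1 only part of a baseline difference carries forward. Chance imbalance at baseline is therefore over-corrected in any one trial, and the variance is larger than when the model estimates the baseline slope. A random-effects model does not remove this by itself: with complete data and a free baseline mean in each arm, it returns the same change-score contrast. It gains efficiency only if baseline is a covariate or the baseline means are held equal, and the article states neither.

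Two things follow. If the randomisation factors are prognostic and left out of the model, the standard errors do not reflect the balance that was built in. And a significance comparison of the arms at baseline tests a hypothesis that randomisation makes true, so it says little about bias and can prompt adjustment chosen after seeing the data.

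At stake are some power and a clear match between the sample size and the contrast it is meant to support.

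**Working it through.** **Inputs** (Sample size calculation): SD 27, alternative SD 20, difference 5 points, alpha 5% (taken as two-sided, which reproduces the article), correlation r = 0.8, 200 per group. The value r = 0.6 used below is an assumption, not a figure from the article.

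**Formula.** n per group = 2 (z_alpha + z_power)² × SD² × f / 5², where (z_alpha + z_power)² is 10.507 for 90% power and 7.849 for 80%, and f is the variance factor of the analysis.

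**Step 1: the article's figures without correlation (f = 1, SD 27).** 2 × 10.507 × 729 / 25 = 612.8, so 613. 2 × 7.849 × 729 / 25 = 457.7, so 458. Both match: "with 5% statistical significance (alpha) and 90% power (beta), the calculated required number of participants in each group is 613 people" and "With 80% power the required number of participants is reduced to 458".

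**Step 2: which analysis gives 160 and 120?** With a common correlation of 0.8 between all measurements and SD 27:

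| Analysis | f | n at 90% | n at 80% |
|---|---|---|---|
| Change score, one follow-up: 2(1 − r) | 0.40 | 246 | 184 |
| Baseline-adjusted, one follow-up: 1 − r² | 0.36 | 221 | 165 |
| Change score, mean of two follow-ups: (1 + r)/2 + 1 − 2r | 0.30 | 184 | 138 |
| Baseline-adjusted, mean of two follow-ups: (1 + r)/2 − r² | 0.26 | 160 | 120 |
| Change score, mean of three follow-ups: (1 + 2r)/3 + 1 − 2r | 0.267 | 164 | 123 |

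Only f = 0.26 gives 160 and 120 exactly. No one-follow-up analysis gives them, at SD 27 or at SD 20.

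**Step 3: the listed contrast at those numbers.** The change score with one follow-up (f = 0.40, SD 27) has 74.5% power with 160 per group and 62.1% with 120, where the article states 90% and 80%.

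**Step 4: power at 200 per group**, from Φ(5 / √(2 SD² f / 200) − 1.96):

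- SD 27, r = 0.8, change score: 5 / 1.708 = 2.928, power 83.3%. Baseline-adjusted: 5 / 1.620 = 3.086, power 87.0%.
- SD 20, r = 0.8: 97.7% against 98.6%.
- SD 27, assumed r = 0.6 (f = 0.80 against 0.64): 54.4% against 63.9%.

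The ratio of the one-follow-up factors is (1 + r)/2. Baseline adjustment therefore saves 10% of patients at r = 0.8 and 20% at r = 0.6.

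**Step 5: the randomisation factors.** Fully crossed they give 2 × 4 × 3 × 5 × 3 × 2 = 720 cells for about 400 patients, so only main effects are workable. As categories these use 1 + 3 + 2 + 4 + 2 + 1 = 13 degrees of freedom. With age, duration and EDSS continuous they use 1 + 1 + 2 + 1 + 1 + 1 = 7. A rough penalty for 13 degrees of freedom multiplies the variance by 397/384. If the factors explain nothing beyond baseline, power falls from 87.0% to 85.9%. If they explain 10% of the residual variance (an assumption), it is 89.2% after the same penalty. The article gives no figure for how prognostic they are.

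**The case against.** The strongest reply is that the comparison list only says which time points are set against each other, while the model is named elsewhere. A regression of change on arm with baseline as covariate gives the same treatment effect as a regression of the six-month value, so the wording does not rule out baseline adjustment. The covariate list may well be in the full protocol or analysis plan, which are not shown. This stands. A reader might infer that the plan excludes the randomisation factors or baseline, but the article is silent on both. The point is that the one contrast it spells out is a plain difference in change.

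A reader might also infer that the change score is biased or the analysis invalid. It is not: under randomisation the contrast is unbiased, and the issue is efficiency. Nor do the figures show that 200 per group is too few for 80% power. At the article's correlation of 0.8, power is above 80% either way, and at SD 20 the difference between methods is under one percentage point.

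The factor 0.26 is worked back from 160 and 120, since the article gives no formula, and a three-follow-up change score comes near at 164 and 123. If baseline adjustment was assumed, that suggests it was intended. This does not rescue the single follow-up: neither form of it gives the stated numbers.

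Finally, the A1 against B1 item does not itself mention a significance test. That word appears under Descriptive analysis, for personal and disease characteristics, and nothing says the result will decide the adjustment. The baseline part is a minor wording point.

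**Conclusion.** The point holds as a matter of efficiency and consistency. The six-month contrast is worded as a difference in change, and no conditioning on baseline, common baseline mean or adjustment for the randomisation factors is stated. At the article's own SD 27 and r = 0.8 the loss is modest, about 4 power points at 200 per group, and about 1 at SD 20. It grows to about 10 points only if the correlation is nearer 0.6, which is assumed here. Any gain from the randomisation factors cannot be sized from the article.

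The sample size mismatch is larger. The 160 and 120 per group fit an analysis averaging two follow-ups, whereas the listed contrast has one. If the two follow-ups meant are six and twelve months (an inference), the second falls after the control arm's usual admission at about eight months, so it cannot serve a comparison with no rehabilitation. These results assume equal variances, one correlation for all pairs of measurements, and no dropout.

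**What to change.** Three changes of wording:

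1. State that the six-month contrast (A5 against B2) is estimated in the mixed model with the baseline value as covariate, or with baseline means constrained equal across arms, plus main effects only of the six randomisation factors, with age, duration and EDSS continuous.
2. Report A1 against B1 and the baseline characteristics by arm descriptively, without significance tests.
3. Restate the sample size for one follow-up. At SD 27 and r = 0.8, baseline adjustment needs 221 per group for 90% power or 165 for 80%; 200 per group gives 87%. State the formula and the correlation used.

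No new data are needed: the baseline values and the randomisation factors are already collected. The cost is a few degrees of freedom, about one power point at most if the factors turn out not to be prognostic.
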